#### Pragmatic trial

In contrast to explanatory trials, which test how an intervention works under optimal conditions, pragmatic trials are designed to evaluate the effectiveness of an intervention in routine practice conditions [34]. Consistent with the pragmatic approach [35], SRT recruits community providers and the families whom they serve. All individual components of the SRT intervention have been established as efficacious and ethical and they are organized around usual clinic practice, allowing for flexibility in procedures, methods, and staffing. Pragmatic components of the SRT trial are summarized in Table 1.

**Fig. 1 Fig1:**
[figure not shown]
SRT flow across systems

**Table 1 Tab1:** Pragmatic Features Employed in SRT Clinical Trial

Feature ^a^	Description
Eligibility	• Providers: Community-based PCPs and EI providers in 4 selected counties
	• Parents: Parents of children 16–36 months old receiving care from an enrolled provider; meet criteria for ASD concerns or No concerns based on study screening interview; English- or Spanish-Speaking; No significant comorbid medical conditions.
Recruitment	• Providers: Recruited from usual care settings; Compensation provided only for research-related activities (e.g., mailing recruitment flyers; completing surveys)
	• Parents: Recruited by participating PCPs and EI providers via: posting flyers in waiting area, handing flyers to parents, and/or sending flyers to all families with age-eligible children (i.e., not otherwise targeted). Compensation provided for completing study surveys.
Setting	• Conducted exclusively within usual care settings
Organization	• Care delivery is consistent with that provided in PCP (i.e., screening; referral) and EI (i.e., assessment; intervention) settings.
	• Study provides training and technical assistance in using evidence-based tools.
	• Study provides compensation to programs for EI providers’ workshop attendance.
	Additional resources provided through the study:
	• PCPs & EIs: Materials about early features of ASD and communicating with parents about ASD concerns.
	• PCPs only: Information about local ASD resources; Hand-held tablets parents use to complete the online M-CHAT-R/F; Access to a REDCap database for obtaining M-CHAT-R/F results; CME and/or MOC credits (at no cost) for workshop and project participation
	• EIs only: Interview probes for eliciting behavioral reports from parents; Telemedicine equipment for receiving online consultation. and feedback; STAT materials and certification at no cost; (4) optional CEU credits for workshops (self-pay).
Flexibility/Delivery	• PCPs & EIs: Freedom to use additional screening, assessment, and/or intervention tools; freedom to use the M-CHAT-R/F, STAT, and/or RIT with non-enrolled families and/or children outside the study age range; freedom to develop their own workflow plans.
	Study-specific expectations:
	• PCPs: Use of the web-based M-CHAT-R/F universally at 18 months; Referral of positive screens to EI programs. Both are consistent with AAP practice guidelines.
	• EIs: Use of the STAT for children referred from PCPs with positive M-CHAT-R/F screens; Use of RIT for children who continue to screen positive for ASD.
Flexibility/Adherence	• Adherence to the intervention protocol (i.e., use of the M-CHAT-R/F, STAT, or RIT) is not required for continued study participation.
	• PCPs & EIs: Adherence is monitored through self-report surveys at predetermined intervals.
	• PCPs only: Use of web-based M-CHAT-R/F is monitored at the practice level through the REDCap database. Office managers are contacted if M-CHAT-R/F use is low or declines, to identify possible technical assistance needs.
Follow-up	• PCPs & EIs: Completion of self-report surveys 3 times over an 18-month period after the training workshops.
	• PCPs only: Monitoring of M-CHAT-R/F use through REDCap database records for 18 months following the training workshop.
Primary outcomes	• Providers: Feasibility, acceptability, and use of the M-CHAT-R/F, STAT, and RIT.
	• Parents: Improvements in overall well-being, health care satisfaction, parenting stress, and parenting efficacy for ASD concerns group.
	• Children: Improved social communication skills and earlier receipt of specialized intervention for children with ASD concerns.
Primary analysis	All data are analyzed using an intent-to-treat model.

^a^ These features are outlined in Loudon et al. [35]

**Table 2 Tab2:** Community Demographics

	Spokane	Yakima	Skagit	Lewis
Distance from diagnostic services in Seattle (miles)	279	143	61	84
Population #	475,735	246,977	118,222	75,621
Population density (#/square mile)	3481	56.4	60.9	31
% with Bachelor’s degree or higher	29%	16%	24%	15%
% infants served by WIC	51%	76%	51%	57%
% White	86%	46%	76%	85%
% Hispanic	5%	46%	17%	9%
% Other (combined)	9%	8%	7%	6%

#### Stepped-wedge cluster RCT design

After a period of baseline data collection in Year 1, each county (“cluster”) was randomly assigned (using random permutation/shuffling by the biostatistician) to one of four time periods during Year 2 when providers received their training in the SRT components (see Fig. 2). Our decision to employ the stepped-wedge design was based on several considerations. First, early feedback from providers revealed that their motivation to participate over a 5-year study period was contingent on their receipt of the SRT training. Second, this approach removes some of the logistical constraints associated with implementing a complex multi-level healthcare system intervention in multiple locations, by allowing us to stagger training activities for each county. Third, this design allows for concurrent comparisons between counties exposed to the SRT model and those not yet exposed; a simple pre-post comparison may be confounded by policy or system changes occurring between the pre-intervention and post-implementation periods. Randomization was at the county level (cluster) rather than at the organizational level within each county to minimize cross-contamination (i.e., providers already trained in one organization exposing the yet-to-be trained providers in another organization to the SRT components).

**Fig. 2 Fig2:**
[figure not shown]
Stepped-Wedge Cluster RCT Study Design. The four counties (C1-C4) are randomized to the timing of their SRT training workshops. Lighter shading indicates the period of Pre-SRT family recruitment and data collection, darker shading indicates the Post-SRT family recruitment and data collection window, and black shading indicates the 3-month training and technical assistance (TA) period for providers

Changes in PCP and EI provider practices are examined using a *within-subjects* approach, by comparing service delivery practices before and after SRT intervention. Parent experiences are examined using a *between-subjects* approach, by comparing a sample of parents recruited prior to SRT intervention (Pre-SRT cohort) to a separate sample of parents recruited after SRT intervention (Post-SRT cohort); parents were not aware of the study design and, as such, did not know what cohort they were in.

### Participant recruitment

Recruitment entailed first identifying interested counties, then identifying PCP practices and EI programs with interested providers, and finally recruiting parent/toddler dyads from the caseloads of the participating PCP practices and EI programs.

#### County selection

Counties were selected for participation based on: (1) demographic diversity; (2) the presence of local champions who facilitated connections between the research team and local providers; and (3) interest from both PCP practices and EI programs. The counties vary on sociodemographic factors (see Table 2).

#### Recruitment and consenting of providers

The research team visited interested PCP practices and EI programs to provide study details and obtain feedback regarding study procedures. Suggestions from providers resulted in adaptations to workshop content, study procedures, survey instruments, and study incentives. Our plan was to partner with 2 PCP practices and 2 EI agencies in each county and enroll a total of 40 PCPs and 80 EI across all 4 counties. PCPs and EI providers were given study consent forms and provided with the opportunity to review them at their leisure, and contact the research team with any questions. PCPs and EI providers who enrolled received compensation for completing surveys at designated intervals ($20/time period).

#### Recruitment, eligibility, and consenting of families

In both the Pre-SRT and Post-SRT implementation periods, two parent-toddler samples are recruited: an “ASD Concerns” sample and a “No Concerns” sample. The ASD Concerns sample, recruited from both PCP and EI settings, comprises toddlers who either have an ASD diagnosis or meet one or more of the following criteria indicating ASD “risk”: (1) behaviorally-based parental concerns about the presence of ASD; (2) behaviorally-based provider concerns (PCP or EI) about the presence of ASD; (3) having an older sibling with an ASD diagnosis; or (4) parental report of a prior positive screen on a validated ASD screening tool. The planned sample size for the ASD Concerns group was 490 families total (245 Pre-SRT and 245 Post-SRT). The No Concerns sample comprises toddlers whose parents do not endorse any ASD or other concerns; this sample is recruited exclusively from PCP practices to characterize health care experiences of families without concerns about their child’s development. The planned sample size for the ASD Concerns group was 70 families total (35 Pre-SRT and 35 Post-SRT. English- and Spanish-speaking families are recruited from the participating PCP practices and EI programs using materials available in both languages.

For PCP practices, families of 16- to 20-month-olds attending the child’s 18-month well-child visit receive a study flyer and a “permission-to-contact” form by the PCP or medical assistant. For EI programs, recruitment occurs in several ways: flyers are posted in waiting areas, recruitment letters are sent to all parents of toddlers in the program within the desired age range (16–35 months), and EI providers give the study flyer and permission-to-contact form directly to families with ASD concerns. Once parents directly reached out or providers sent the completed permission-to-contact forms, the study personnel conduct a structured telephone screening interview to determine study eligibility and group assignment.

Parents who were interested and eligible to participate were either mailed or emailed copies of the study consent materials. They were provided the opportunity to review the forms at their leisure, and were instructed to call the research team with any questions or concerns. For parents with literacy issues, research staff members guided them through the consent information and provided them the opportunity to verbally ask questions and consent to the study over the phone. Similar to providers, parents who enrolled received $20 compensation for completing surveys at designated intervals.

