### Designing a new service delivery model for ASD: the screen-refer-treat model

The Screen-Refer-Treat (SRT) model employs state-of-the-art developments in ASD detection and intervention and capitalizes on a readily accessible service delivery infrastructure [20]. The goal of the SRT model is to use a preventive intervention approach and mitigate emerging ASD behaviors during a critical period of development. This model introduces a significant shift in the conceptualization and implementation of ASD services by: (1) offering an ASD-specialized intervention to toddlers when ASD is first *suspected*, rather than waiting until a formal ASD diagnosis is conferred; (2) involving *two integral and interrelated parts of the service delivery system—*primary care and early intervention (EI)—to increase care coordination (See Fig. 1); and (3) addressing obstacles associated with early detection and intervention through the *use of technology* to expedite screening. Two stages of screening are used: Stage 1 (designed for primary care settings), and Stage 2 (designed for referral settings) [21].

The SRT model comprises three components: PCPs conduct universal Stage 1 ASD screening at the 18-month well-child visit (Screen); PCPs immediately refer toddlers who screen positive to a community-based EI program (Refer); and EI providers initiate ASD treatment (Treat) after verifying ASD risk with a Stage 2 screen.

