### Study aims

This pragmatic trial was designed to test the effectiveness of the SRT model in improving both system-level and family-level outcomes. At the *system level*, our aims are to: (1) increase the number of toddlers receiving ASD screening at their 18-month well-child visit; (2) increase the number of toddlers with positive screens who receive evidence-based behavioral intervention prior to age 3; (3) reduce the length of time between parents’ expressed concerns about ASD and the child’s receipt of ASD-specialized intervention; and (4) reduce disparities in identification of ASD for Hispanic families, given the magnitude of the delays they experience relative to other underrepresented populations [2]. At the *family level*, the SRT project aims to: (1) improve parents’ well-being, parenting efficacy, parenting stress, and health care satisfaction; and (2) improve children’s social-communication skills. This paper describes how the SRT trial was designed and is being conducted, highlighting successes and challenges we have encountered during trial implementation.

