##### Screen and referral training for PCPs.

Training for PCPs comprises two components. The first is a 2-h onsite workshop for each practice. Training emphasizes the rationale and processes for recognizing the early behavioral features of ASD, conducting universal screening at 18 months, using the web-based M-CHAT-R/F, and discussing positive screens and appropriate referrals with parents. Tablets and WiFi “hotspots” are provided to each practice. The second component involves an onsite TA visit to each practice 2 weeks later, to train office and medical staff on using the web-based M-CHAT-R/F system and developing an optimal work flow plan to accommodate the new procedures. Work flow plans delineate: (1) who is responsible for handing parents the tablet containing the web-based M-CHAT-R/F, and collecting it when completed, (2) when and where the tablet will be given to parents (e.g., waiting area vs. exam room), (3) how the M-CHAT-R/F results are displayed on the final screen, and (4) how the results are conveyed to the PCP. The research team remains “on-call” for TA requests and works with office staff to monitor progress and detect barriers to implementation.

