##### Assessment and treatment training for EI providers.

Training for EI providers occurs through two one-day workshops, both involving “hands-on” practice with children. The STAT workshop provides training on the STAT and a developmentally-targeted parent interview to identify ASD risk. Information about discussing ASD with parents is also included. The RIT workshop provides training on using RIT with toddlers at ASD risk, as well as coaching parents in the use of RIT. WiFi hot spots and video recording equipment are provided to each program to enable them to receive performance feedback and online coaching for the STAT and RIT.

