Additionally, while our original plan was to recruit two groups of families (i.e., those with ASD Concerns and those with No Concerns), it became apparent that both PCPs and EI providers were hesitant to talk to parents about a study that referred to “ASD concerns.” Even when EI providers had ASD concerns about children, they were reluctant to share their concerns with families until it was time for the child to transition out of EI services into school services. Several adaptations were made in an effort to increase recruitment of the ASD Concerns group. First, the criteria for study eligibility were broadened to include a third group of toddlers for whom there were concerns about more general developmental delays. Second, we provided sample scripts and conducted in-person coaching with EI providers about how to introduce the study to parents in an encouraging manner. Third, we extended the recruitment period beyond the initial 6-month window. Although these measures were somewhat effective, our recruitment numbers for the ASD Concerns group remain lower than projected. With only a quarter of sample size as we initially planned, the power to detect our projected effect sizes on many outcomes will be seriously reduced. Still, we plan to carry out all the planned analyses. But the inference will be interpreted with caution. Instead of treating the analysis as confirmatory, we will focus on the direction and magnitude of the effect sizes, which will serve as effect size estimates for future, well powered, confirmatory studies. In addition, the current sample size should still provide enough power (> 90%) to detect an absolute increase of 30% in level-2 screening in EI Pre- vs. Post-SRT periods.

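### The ASD Concerns group is defined partly by screening results and provider concern, which SRT can change, so the Pre and Post family cohorts may differ in case mix without any SRT effect

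*Protocol article*

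**What the plan says.** Under *Recruitment, eligibility, and consenting of families*, a toddler joins the ASD Concerns sample with an ASD diagnosis or any one of four risk criteria. The first is parental concern. The others are "2) behaviorally-based provider concerns (PCP or EI) about the presence of ASD", "3) having an older sibling with an ASD diagnosis" and "4) parental report of a prior positive screen on a validated ASD screening tool". A structured telephone interview after referral settles eligibility and group.

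The intervention acts on the same things. In the model description, "PCPs conduct universal Stage 1 ASD screening at the 18-month well-child visit (Screen". The first system-level aim is to "increase the number of toddlers receiving ASD screening at their 18-month well-child visit". PCP training covers "discussing positive screens and appropriate referrals with parents". For the EI workshop on the STAT, "Information about discussing ASD with parents is also included".

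The end of *Stepped-wedge cluster RCT design* says that parent experience is compared between one sample recruited before SRT and a separate sample recruited after it. Table 1 ties the parent and child primary outcomes to the ASD concerns group. *Recruitment and retention of pre-SRT families* says of EI providers who did have ASD concerns that "they were reluctant to share their concerns with families until it was time for the child to transition out of EI services". It also reports that a third group, DD Concerns, was added to help recruitment.

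**The concern.** The family comparison conditions on a label that the intervention can alter. Universal screening produces more parent-reported positive screens (criterion 4). Training in recognition makes provider concern more likely (criterion 2). Training in disclosure can raise parental concern (criterion 1) and, further on, diagnosis. Only the older-sibling criterion is clearly outside SRT's reach.

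A child whose EI provider kept quiet about ASD before SRT could have been placed in DD Concerns or No Concerns, or never recruited. The same child could be in ASD Concerns after SRT. Group means for social communication, parenting stress, well-being, satisfaction and age at specialised services could then move because membership moved.

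This matters more because the authors now intend to read the direction and magnitude of these effects as estimates for later trials. A small sample widens the interval, whereas a case-mix shift displaces the estimate itself.

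**Working it through.** **Which safeguards reach the problem.** Randomised county timing guards against calendar-time change, but not against selection after a county is trained. Intent-to-treat (Table 1) governs how recruited families are analysed, not who is recruited. The statement that procedures are identical for both cohorts sits under *Parent measures*, and identical criteria do not help when SRT changes who meets them. Parents not knowing their cohort is beside the point, because providers and screens generate the label. Flyers and letters to all families soften selection into contact, but not classification.

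**Detectable difference.** The plan says only that small to moderate differences are detectable at 80% power. It gives no effect size in SD, alpha or ICC, so its figure cannot be reproduced. Assuming two-sided 5% and no clustering, d = (1.960 + 0.842) × √(2/n):
- n = 245 per cohort (planned): 2.802 × √(2/245) = 0.253 SD
- n = 65 per cohort (actual Pre number, assumed for Post too): 2.802 × √(2/65) = 0.491 SD
- n = 245 with an assumed design effect of 1.5 to 3: 0.31 to 0.44 SD

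**Bias through criterion 4 alone.** Let s be the Pre share of children eligible only through a prior positive screen, r the growth of that inflow, and D the outcome difference in SD between these children and the rest. Then Post share = s·r / (1 − s + s·r), and bias = (Post share − s) × D.

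The values of s (10 to 40%) and D (0.3 to 0.8) are assumptions. For r, *Statistical analyses and power* takes 50% of PCPs as screening universally and a 22-point detectable change, so r = 72/50 = 1.44. Moving to fully universal screening gives r = 100/50 = 2. Type I error is that of a two-sided 5% test with 245 per cohort and no clustering.

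| s | r | D | Post share | Shift | Bias (SD) | Share of 0.253 | Type I error |
|---|---|---|---|---|---|---|---|
| 10% | 1.44 | 0.3 | 13.8% | 3.8 points | 0.011 | 4% | 5.2% |
| 20% | 2 | 0.5 | 33.3% | 13.3 points | 0.067 | 26% | 11% |
| 40% | 2 | 0.8 | 57.1% | 17.1 points | 0.137 | 54% | 33% |

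**Wider assumptions, all routes.** Let f be the share of Post children who would not have qualified Pre (0.2 to 0.5, assumed) and d their difference in SD (0.5 to 1.0, assumed). Bias = f × d runs from 0.2 × 0.5 = 0.10 to 0.5 × 1.0 = 0.50 SD.

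**Entry age.** In Table 5 the Pre ASD Concerns children entered at a mean of 27.63 months. The No Concerns children, planned to come only from PCP practices, entered at 20.56. If 30% of Post children (assumed) entered at the latter age instead of the former, mean entry age would fall by 0.3 × (27.63 − 20.56) = 2.1 months. Surveys stop at 36 months, so mean available follow-up would grow from 36 − 27.63 = 8.4 to about 10.5 months.

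**The case against.** The strongest reply is that no Post-SRT family data exist in this article, so any difference in case mix is a prospect and not an observation. That stands.

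A reader might go further and infer that Post children will be younger and milder, so that the bias favours SRT. The documents do not support a direction. The *Screen* section says that skipped follow-up questions raise false positives in usual practice and that the web-based tool triggers those questions automatically. Post positives could therefore be truer and more severe. Younger children may also score lower on an age-dependent social-communication measure, which would count against SRT.

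A reader might also infer that the bias equals the whole detectable effect. That follows only from particular choices: 0.3 × 0.8 = 0.24 SD against 0.253 SD. Neither input is in the documents, and at 65 per cohort 0.24 SD is about half of 0.491 SD.

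Nor is every family recruited with its county's schedule already known. Assignment followed a Year 1 baseline period, so part of the Pre cohort came first.

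Pooling ASD and DD Concerns as the main group may look like a cure. It removes movement between those two labels only, leaves inflow from No Concerns and from children previously missed, and replaces the population named in Table 1.

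Finally, covariates and sensitivity analyses usually belong in an analysis plan that is not shown, and their absence here is not the point. The eligibility rule that creates the need for them is fixed in this article. The authors' move to a non-confirmatory reading answers low power, not this bias.

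**Conclusion.** The point holds for the family and child comparison of the ASD Concerns cohorts. Criteria 2 and 4 are directly open to change by SRT; criterion 1 and diagnosis are open indirectly. The cohorts may differ in case mix and entry age with no SRT effect.

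Size and direction cannot be computed from the documents. The illustrations run from negligible (0.01 SD) to 0.14 SD through criterion 4 alone, and to 0.5 SD under wider assumptions, with a possible fall of about 2 months in mean entry age. All of these rest on assumed shares and differences.

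The point does not extend to provider outcomes, which are compared within subjects, or to the PCP Checklist, which is completed for all 18-month visits whether or not the family takes part. It does not show that the trial's results will be wrong. It is an inexpensive improvement worth making before the Post cohort is classified.

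**What to change.** Keep ASD Concerns as the main group and make these changes:
- Record every qualifying criterion for each family at the existing telephone interview. For Pre families, recover this from interview records and the Child Health Services Survey where available.
- Model child outcomes with age at survey as the time axis, and adjust the Pre/Post comparison for recruitment source (PCP or EI) and child sex.
- Report Pre and Post case mix side by side: qualifying criteria, source, entry age and sex.
- Add two sensitivity analyses: (a) excluding children who qualify only through criterion 2 or 4; (b) pooling ASD and DD Concerns (65 + 68 = 133 Pre families).
- State that these steps reduce the bias but do not remove it, and interpret the family-level effect sizes accordingly. Analysis (a) still leaves criterion 1 and diagnosis open to SRT, and (b) does not stop inflow from No Concerns or from children previously missed.

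The cost is one recorded item and a little more analysis. Recruitment source, age and sex are already held. The restricted analysis will have smaller numbers. The pooled analysis dilutes an ASD-specific effect and includes a group added part-way through recruitment.
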